## 1.10 Summary of changes to protocol

1. Expanded the eligibility criteria to include patients 60 years of age with earlier stages of cardiac, pulmonary or oncologic diseases if they had at least one prior hospitalization during the past year.

2. After the first 20 patients were enrolled, we added a question about general life satisfaction, a question about perceived life expectancy, a question about extent of prior deliberation on end-of-life care, a question about preference for general approach to treatment in the event of serious illness, and a modified time tradeoff question designed to understand whether patients would trade time alive to avoid ICU care at the end of life

3. Obtained a waiver of consent for collection of information regarding whether there is a living will in the electronic medical record for all patients approached to participate in the study, including those who do not consent. For all patients approached, including both those who do and do not consent, we collected information from the electronic health record for the University of Pennsylvania Health System regarding whether there is a living will for that patient on file.

4. We relaxed the requirement for a second visit to obtain the health state evaluations to facilitate complete data capture. Patients in the deliberative arm were still required to wait for at least 1 minute prior to making health care choices, but in both arms we allowed complete data capture to occur during the same visit.

## 2 Statistical analytic plan

The primary outcome will be the choices patients make whether to accept or decline the life-sustaining interventions. The primary exposure will be whether participants were responding in the intuition or the deliberation arm. Chi-square testing will be used to compare these arms. In secondary analyses, we will evaluate congruence between stated valuations of health states and treatment acceptance or refusal, which will be intended as a proxy for decision quality. We will use a logistic regression model to determine how valuations of relevant health states influence the refusal or acceptance of treatments; the resulting odds ratio will represent the incremental odds of refusing treatment with one unit increase on the valuation scale. Because we are interested in the relationship between the scale and treatment refusal across groups defined by randomization, we will additionally explore an interaction between scale and randomization group. Finally, we will analyze the difference between the means of the two randomization groups on the state anxiety scale and the uncertainty subscale of the Decisional Conflict Scale. These data will be described using means and t-tests if normally distributed or medians and Wilcoxon rank sum tests if not normally distributed.

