### 1.3.3 Target population

We will be recruiting 200 patients aged 60 or older with chronic respiratory, oncological or cardiovascular diseases. This sample size would provide at least 80% power to detect differences of 20% above or below baseline rates of 50% in the proportions of patients choosing each form of life support

or goal of care with a type I error rate of 0.05. Power to detect the same 20% absolute effects would increase if baseline rates deviate away from 50%.

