#### *1.3.5 Method for assigning subjects to groups*

Consenting subjects will be randomized with a 50% probability to each trial arm (intuitive versus deliberative procedures) using Qualtrics. The research coordinator/PI will become unblinded to the patients allocation when they open the electronic survey

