### 1.7.2 Procedures

The research coordinators will screen electronic medical records of inpatients on the general medicine, pulmonary, cardiology and oncology wards at the Hospital of the University of Pennsylvania for eligibility. Patients' eligibility status will be entered into the eligibility database. We will record ICD9 and ICD 10 codes. Eligible patients will be approached by a research coordinator in the inpatient setting who will seek patients consent to participate in a study exploring patient decision making about life-sustaining medical treatments. The research coordinator will specify that the questions are hypothetical and that the answers are not binding, but emphasize that we would like patients to answer the questions as if they were real. Following discussion of the study, research coordinators will obtain written consent from patients. The consent forms will contain HIPAA statements of authorization of release of medical records, thus facilitating our collection of data from medical and billing records during the study. The consent includes clear explanations that different types of decision making will be assigned by chance. The research coordinators will explain who will be enrolled, how many patients are being targeted for enrollment, and what the outcomes of interest are.

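### The primary chi-square is valid but unadjusted and gives no effect size; an adjusted risk difference with a 95% CI would add modest precision from baseline information the study collects

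*Combined protocol and SAP*

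**What the plan says.** Section 2 defines the outcome: "The primary outcome will be the choices patients make whether to accept or decline the life-sustaining interventions". The only arm comparison stated for it is "Chi-square testing will be used to compare these arms". The logistic model in the same section relates health-state valuations to refusal, with an exploratory interaction by arm; it is not an adjusted analysis of the arm effect.

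Section 1.3.5 gives the allocation: "Consenting subjects will be randomized with a 50% probability to each trial arm". No blocks or strata are described, so it reads as simple randomisation.

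Three kinds of baseline information appear elsewhere:

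- **Disease.** Sections 1.7.2 and 1.7.3 say, in describing screening, "We will record ICD9 and ICD 10 codes".
- **Living will.** Section 1.10, item 3, covers everyone approached: "we collected information from the electronic health record for the University of Pennsylvania Health System regarding whether there is a living will".
- **Age.** Section 1.3.3 sets it as an entry criterion: "We will be recruiting 200 patients aged 60 or older with chronic respiratory, oncological or cardiovascular diseases". It must therefore be known at screening, but section 1.4 does not name it among the survey items.

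Section 2.1, item 1, adds interactions between arm and prior living wills or goals-of-care conversations on the primary outcomes.

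On power, section 1.3.3 states "This sample size would provide at least 80% power to detect differences of 20% above or below baseline rates of 50" per cent, "with a type I error rate of 0.05".

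**The concern.** The sample mixes three disease areas and, under section 1.10, item 1, was widened to earlier-stage disease. Willingness to accept life support may well differ by disease, age and prior planning. An analysis that ignores such variables leaves the variation they explain in the error term. Simple allocation of 200 patients also does nothing to even these variables out between arms.

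Two things are at stake. The first is precision: calculated power is less than 3 points above the stated minimum. The second is interpretation. A chi-square gives a p-value but does not show which differences a non-significant result rules out. Section 2.1, item 2, records that the investigators themselves wanted more than p-values once they had seen the results.

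**Working it through.** **Inputs.** From section 1.3.3: 200 patients (taken as 100 per arm), 50% v 70%, alpha 0.05. Sidedness is not stated; two-sided is assumed. No dropout allowance is stated and none is applied. The prevalence, prognostic strength and R² used below are assumptions, because the documents give none.

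**1. The plan's own figure.** The pooled rate is 0.60.

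- SE under the null = √(2 × 0.6 × 0.4 / 100) = 0.0693
- SE under the alternative = √((0.5 × 0.5 + 0.7 × 0.3) / 100) = 0.0678
- z = (0.20 − 1.96 × 0.0693) / 0.0678 = 0.947, so power = 82.8%

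The result for 50% v 30% is the same. The stated minimum of 80% is met. With 50% allocation the central 95% range of arm size is 86 to 114; averaging over random arm sizes gives 82.6%.

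**2. Validity of the unadjusted test.** The type I error of the uncorrected chi-square, averaged over random arm sizes at a 50% rate, is 5.2%.

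**3. Size of chance imbalance.** For a binary factor with prevalence q, the SD of the between-arm difference is √(q(1−q) × 4/200). With q assumed 33%, this is √(0.33 × 0.67 × 0.02) = 6.65 points, and 1.96 SD is 13 points. The observed arm difference moves by imbalance × gap in acceptance between holders and non-holders:

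- assumed gap 10 points: 0.13 × 10 = 1.3 points
- assumed gap 30 points: 0.13 × 30 = 3.9 points

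The design difference is 20 points. An imbalance of 10 points or more has a probability of about 13% at this prevalence.

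**4. What such a factor explains.** R² = q(1−q) × gap² / (0.5 × 0.5).

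- gap 10 points: 0.2211 × 0.01 / 0.25 = 0.9%
- gap 30 points: 0.2211 × 0.09 / 0.25 = 8.0%

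Steps 3 and 4 describe the same quantity in two ways. The imbalance shift is the part of the sampling error that adjustment takes out, so it should not be counted as a second benefit.

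**5. Gain from adjustment.** Effective N = 200 / (1 − R²), put into the formula in step 1. The 95% CI half-width is 1.96 × 0.0678 × √(1 − R²).

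| Assumed R² | Effective N | Power, 50% v 70% | CI half-width (points) |
|---|---|---|---|
| 0 | 200 | 82.8% | 13.3 |
| 1% | 202 | 83.2% | 13.2 |
| 5% | 211 | 84.7% | 13.0 |
| 10% | 222 | 86.6% | 12.6 |
| 15% | 235 | 88.4% | 12.3 |

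**6. Check by simulation.** 4,000 trials per setting compared the chi-square with the Wald test of arm in a logistic model containing living will, age and disease group. The standardised risk difference itself was not simulated.

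| R² | Unadjusted power | Adjusted power |
|---|---|---|
| 0 | 82.6% | 82.4% |
| about 2% | 83.6% | 83.7% |
| about 5% | 82.4% | 83.9% |
| about 11% | 82.9% | 86.4% |
| about 18% | 82.7% | 88.4% |

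Type I error was 5.2% to 6.0% unadjusted and 5.2% to 5.6% adjusted, with a Monte Carlo SE of about 0.3 points. Covariates that predict nothing cost 0.2 points of power, which is within simulation error.

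**The case against.** The strongest reply is that nothing here is wrong. An unadjusted chi-square is a conventional and valid test for a pilot randomised trial. Its error rate already allows for chance imbalance, and the stated power is met. All of that stands.

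The gain also depends on an R² that nobody has given. With weak covariates it disappears: near 1%, power rises by about 0.4 points. That stands too, and is why the table starts there. Reporting a risk difference with a CI does not itself require adjustment, which is also true.

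The covariates are less ready for use than they may look. Age is documented only as an eligibility limit. ICD codes are mentioned with the eligibility database, and no disease-group variable is defined. Section 1.7.3 does not list either by name among the items entered in the analytic database, and the identifier link is destroyed once a patient's interviews end. The timing of the living-will chart review relative to randomisation is not given. These are conditions on the fix, not reasons against it.

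A reader might infer more than the documents support:

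- **That chance imbalance biases the comparison.** It does not; randomisation makes the unadjusted difference unbiased. Adjustment reduces the error conditional on the imbalance that happened to occur.
- **That living-will information goes unused.** Section 2.1, item 1, uses such information in interactions. Those analyses ask whether the effect varies and leave the overall arm effect unadjusted.
- **That the living-will flag records the preference being measured.** Section 1.10 records only whether a document is on file, not what it says.
- **That the power claim fails.** A continuity-corrected chi-square would have 79.2% exact power, but the plan does not specify a correction.
- **That allocation should now be stratified.** Sections 1.10 and 2.1 describe enrolment and review of results in the past tense; a new randomiser setting cannot rebalance patients already allocated.

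**Conclusion.** The point holds as an efficiency improvement, not as an error in the plan. The primary comparison is valid and adequately powered on its own terms, but it yields no effect size and makes no use of baseline predictors in estimating the overall arm effect.

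The gain is about 0.4 points of power if R² is 1%, about 2 points at 5%, about 4 at 10% and between 5 and 6 at 15%. The 95% CI half-width shrinks from 13.3 to between 13.2 and 12.3 points. These figures assume equal arms of 100, two-sided alpha of 0.05, no missing data, and an R² range that the documents neither support nor exclude. The gain in interpretation, an estimate with an interval, does not depend on R².

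**What to change.** Amend section 2 as follows.

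- **Estimate.** For each life-support choice, report the adjusted risk difference (deliberative minus intuitive) with a 95% CI. Fit a logistic regression on arm, chart living-will status, disease group and age, standardise over the whole sample, and use a robust standard error. Keep the chi-square beside it.
- **Covariates.** Define disease group from the ICD codes, with a rule for patients who fall in more than one. Use living-will status as at randomisation, from the chart: the survey question about such documents is asked after the treatment choices.
- **Data flow.** State that age, disease group and chart living-will status are carried into the analytic dataset before the identifier link is destroyed. If the link has gone and a variable was not carried over, adjust for those that are held and say so.
- **Status.** If the analysis is added after results were reviewed, label it post hoc and supportive.
- **Rare choices.** If few patients accept or decline an intervention, the model may be unstable; name in advance a smaller covariate set for that case.

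The cost is a paragraph in the plan, a coding rule for the ICD codes, a few lines of code and the data carry-over. No further patient contact is needed, and allocation stays as it is.

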#### Health state valuation questions:

We will ask a series of questions designed to understand how the patient values various health states. We will use three distinct health states: the patient's current state of health and two hypothetical health states that span four domains - cognitive functioning, physical mobility, self-care and pain/discomfort. We will first ask the patient to rate each state of health on a 10-point Likert scale with 0 being much worse than death and 10 being much better than death. We also will ask patients to evaluate a variety of single item health states on a visual analog scale ranging from worst state of health imaginable to best state of health imaginable.

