*Pilot Testing:* During pilot testing, we will test several methods for encouraging patients in the intuitive arm to answer the questions based on intuition including: (a) a time constraint condition, under which patients will be asked to make a decision about the four hypothetical questions based on gut instinct and to answer each question within one minute; and (b) a cognitive loading condition, under which patients will be asked to attend to a second task while also reading the hypothetical scenarios and answering the questions about whether they would or would not want the therapy in question. The second task will either be retention in working memory of a string of numbers or a task that involves pressing a button every time a specific number appears on the bottom of the computer screen. We will ask patients in each condition how difficult the task was to verify that the cognitive load group found the task significantly harder than the other groups. We will also administer a test of analytical reasoning to groups in the various pilot arms to establish that time constraint and cognitive load result in lower ability to engage in analytical reasoning than the group without a time constraint or a cognitive load. The tests we will use to assess analytical reasoning include denominator neglect questions, belief bias syllogisms and the Cognitive Reflection Test. We will also pilot test doing the interviews for both arms in a single survey session and in two separate sessions separated by as much as 24 hours. Once we determine during pilot testing the logistics of how we will organize the intuition and deliberation arms, we will submit a modification describing the final proposed technique.

The questions will be administered as a Qualtrics survey, facilitated by the research coordinator. At this point, we anticipate that patients in each arm will have two facilitated survey sessions with the research coordinator, as follows (although we may do a single session for one or both arms depending on the results of the pilot testing).

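### The Aim 2 logistic model leaves open whether a patient's four choices are pooled; if pooled without clustering its interaction test would be anti-conservative, and equal slopes would not show equal congruence

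*Combined protocol and SAP*

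**What the plan says.** SAP section 2 gives the only analysis of Aim 2, as a secondary analysis: "We will use a logistic regression model to determine how valuations of relevant health states influence the refusal or acceptance of treatments". The result is a single odds ratio of refusal per unit of the valuation scale. The SAP will also explore an interaction between that scale and randomized arm. It presents the analysis as an evaluation of congruence, standing in for decision quality.

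Each patient supplies several choices and several ratings. Section 1.7.2 has patients "make a decision about the four hypothetical questions based on gut instinct", and section 1.4 lists feeding tubes, dialysis, antibiotics and ventilation as the subjects. Section 1.4 also has three health states rated on a scale "with 0 being much worse than death and 10 being much better than death", plus single-item states on a visual analog scale.

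The SAP does not say:
- whether the four choices enter one model or four;
- which rating, on which scale, is relevant to which choice;
- how correlation within a patient would be handled;
- what makes a single choice congruent.

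**The concern.** There are two separate issues.

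**Clustering.** One model and one odds ratio for several treatments can be read as a stacked data set with four rows per patient. Ordinary logistic regression takes rows as independent. A patient's general attitude to life support plausibly affects all four answers. If the ratings are also similar within a patient, the model-based standard errors for the slope and its arm interaction would be too small. A chance difference between arms could then be reported as a difference in decision quality.

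**Meaning of the slope.** The odds ratio per point says how steeply refusal changes with the rating. It does not say where on the scale patients switch from refusing to accepting. Two arms with the same slope and different switching points have zero interaction, although one arm's choices may match its own ratings less often. Reading a null interaction as equal congruence would be wrong in that case.

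**Working it through.** **Inputs from the documents.** Section 1.3.3: "We will be recruiting 200 patients aged 60 or older", planned "with a type I error rate of 0.05" (two-sided assumed). Section 1.3.5: "Consenting subjects will be randomized with a 50% probability to each trial arm", so about 100 per arm. Four choices per patient (section 1.7.2). Ratings from 0 to 10 (section 1.4).

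**The plan's own figure.** The only stated power concerns the primary comparison: at least 80% for a 20-point difference from 50%. Power = Φ[(d − 1.96·SE0)/SE1], with SE0 = √(2·p̄(1−p̄)/n) and SE1 = √([p1(1−p1)+p2(1−p2)]/n). For 0.50 v 0.70 and n = 100: SE0 = √(2·0.6·0.4/100) = 0.0693, SE1 = √(0.46/100) = 0.0678, and (0.20 − 0.1358)/0.0678 = 0.947. Power is 82.8%, so the claim reproduces. No figure is given for Aim 2.

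**Clustering: simulation.** 200 patients, 3,000 runs per cell, no true interaction. Log-odds of refusal = −0.2·(rating − 5) + patient effect. Ratings are normal around 5 with SD 2.5, rounded and limited to 0–10. Latent ICC = σ²/(σ² + 3.29), so σ = 1 gives 0.23 and σ = 1.81 gives 0.50. The ICC, the slope and the within-patient correlation of ratings are assumptions; the documents give none of them.

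Rejection of the interaction at nominal 5%, four choices pooled (ordinary / patient-clustered standard errors):

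| Latent ICC | Rating correlation 0 | 0.5 | 1 (one shared rating) |
|---|---|---|---|
| 0 | 4.6% / 4.8% | 5.3% / 5.4% | 5.1% / 5.3% |
| 0.23 | 5.5% / 5.7% | 7.7% / 4.9% | 11.4% / 5.3% |
| 0.50 | 4.5% / 4.6% | 11.4% / 5.4% | 17.7% / 5.9% |

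Monte Carlo error is about 0.4 points near 5% and √(0.177·0.823/3000) = 0.7 points in the last cell. Independent repeats of that cell gave 17.9% and about 19%. With one model per treatment the ordinary test rejects in 5.2% to 5.5%. Inflation therefore needs pooling, correlated choices and correlated ratings together.

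**Slope against congruence: worked example.** Take log-odds of refusal = a − 0.4·(v − 5) in both arms, with ratings v uniform on 0, 1, …, 10. The switching point is 5 + a/0.4. Count a choice as congruent if it is refused with v < 5 or accepted with v > 5, and leave out v = 5.

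- Arm with a = 0 (switches at 5): refusal at v = 0–4 is 0.881, 0.832, 0.769, 0.690, 0.599 (sum 3.77). Acceptance at 6–10 mirrors it (3.77). Congruent: 7.54/10 = 75.4%.
- Arm with a = 2 (switches at 10): refusal at 0–4 is 0.982, 0.973, 0.961, 0.943, 0.917 (sum 4.78). Acceptance at 6–10 is 0.168, 0.231, 0.310, 0.401, 0.500 (sum 1.61). Congruent: 6.39/10 = 63.9%.

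The true interaction is exactly 0. Refusal of states rated above the midpoint is 24.6% in the first arm and 67.8% in the second.

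**Would the primary analysis show it?** Overall refusal in the example is 50.0% v 82.2%. The power formula with n = 100 gives (0.322 − 1.96·0.0669)/0.0630 = 3.03, or over 99%. For a smaller shift (a = 1, switching at 7.5), congruence is 71.8% v 75.4% and refusal 67.7% v 50.0%: (0.177 − 1.96·0.0696)/0.0685 = 0.59, about 72% power on a single item.

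**The case against.** A reader might infer that the SAP treats the four choices as independent and that its interaction test is therefore anti-conservative. The documents do not support that. The SAP never says that the choices are pooled or that rows are independent. Section 1.3.3 plans power item by item, for each form of life support or goal of care, which suits one model per treatment. That reading brings no inflation within each test. It does bring four interaction tests: if they were independent, 1 − 0.95⁴ = 18.5% would be the chance of at least one false positive.

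It is also tempting to quote only the shared-rating column. The reference to relevant health states suggests ratings matched to scenarios, for which a correlation below 1 is more natural. The range has to be shown.

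On the slope, a shift in switching point large enough to matter also changes acceptance, and the planned chi-square tests would usually find it. So the difference would not go unseen. But it would be reported under Aim 1, and nothing in the SAP would lead anyone to read it as a difference in congruence.

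Finally, a midpoint rule is not neutral. The documents label only the ends of the scale, and a patient who refuses treatment for a state rated above 5 may be weighing the burden of treatment. Aim 2 asks how choices map onto values, which a measure of association partly answers. This limits the congruence share to a supportive role; it does not make equal slopes mean equal congruence.

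**Conclusion.** The point holds as a conditional one on clustering and a general one on interpretation.

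- If choices are pooled in an ordinary logistic model, the interaction's type I error is about 8 to 12% at a rating correlation of 0.5 and about 11 to 19% with one shared rating, for an assumed latent ICC of 0.23 to 0.5. It is near 5% with uncorrelated ratings or separate models. Patient-clustered standard errors bring it to 4.6% to 5.9% in the table.
- Under either reading of the SAP, a null interaction does not establish equal congruence. The 75.4% v 63.9% example depends on the assumed slope, rating distribution and midpoint. The zero interaction follows from the equal slopes alone.

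The analysis is secondary and the interaction exploratory, in a trial that section 1.3.1 calls a pilot. The primary comparison and sample size are not touched. The change is worth making because Aim 2 has no other analysis.

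**What to change.** In SAP section 2:

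1. State which health-state rating, on which scale, is paired with each of the four choices, and whether choices are pooled or modelled one treatment at a time.
2. If pooled, fit logistic regression by GEE with patient as cluster, scenario as a fixed factor and robust standard errors. A patient random intercept is an alternative, but its odds ratio is patient-specific rather than population-averaged, so choose one in advance. Report the valuation-by-arm odds ratio with its 95% CI as the exploratory Aim 2 result.
3. If modelled by treatment, say so and report all four interactions together.
4. Add a supportive analysis: each patient's proportion of congruent choices (accepted with a rating above the midpoint, refused with one below it, midpoint ratings excluded), compared between arms, with other cut-points as sensitivity analyses.
5. State that similar slopes will not be reported as similar congruence.

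The cost is SAP wording and a little code, with no new data. Intervals would be somewhat wider, and the supportive measure rests on an assumed midpoint. Section 2.1 records that results have already been reviewed, so for this trial the change should be dated and labelled post hoc.
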